## Abstract

**Introduction:**

Functional constipation (FC) is a common functional gastrointestinal disorder in clinical practice, with the prevalence of which increasing with age. With the increasing aging of the population worldwide, this problem is bound to become more prominent. Acupuncture is effective and recommended for the treatment of FC. However, little is known about how acupuncture affects the gut microbiota and inflammatory cytokines and thus improves gut function. Meanwhile, there are few high-quality clinical trials specifically focusing on acupuncture in treating FC in older people. The objective of this study is to assess the efficacy and safety of acupuncture in treating FC in older people. Additionally, the research aims to explore the mechanism of action of acupuncture in treating FC in older people by affecting intestinal microbiota and inflammation cytokines.

**Methods and analysis:**

This study is designed as a single-center, randomized, sham-controlled clinical trial. A total of 98 eligible FC patients will be randomized in a 1:1 ratio into an acupuncture group and a sham acupuncture group. Both groups will receive 24 treatments over 8 weeks with a 12-week follow-up. The primary outcome of the study is the treatment response rate, which is the proportion of participants with ≥3 mean weekly Complete Spontaneous Bowel Movements (CSBMs) over weeks 3–8. The secondary outcomes will include the proportion of participants with ≥3 mean weekly CSBMs during other assessment periods; the percentage of patients with ≥1 increase in mean weekly CSBMs from baseline; the average changes in CSBMs; Patient Assessment of Constipation-Symptoms (PAC-SYM), Bristol Stool Scale, Patient Assessment of Constipation Quality of Life Questionnaire (PAC-QOL), Self-rating Anxiety Scale (SAS), Self-rating Depression Scale (SDS) and weekly usage of emergency bowel medications. Adverse events will be recorded throughout the study. Data for the outcomes will be collected at Week 0 (baseline), Week 4 (the intervention period), Week 8 (the post-treatment), Week 12 (the follow-up period) and Week 20 (the follow-up period). In addition, changes in intestinal microbiota will be analyzed using 16S rRNA high-throughput detection, and the concentration of relevant inflammatory cytokines in serum will be measured by ELISA based on blood samples. The intention-to-treat analysis will be performed in this study.

**Clinical trial registration:** [https://www.chictr.org.cn/], identifier [ChiCTR2300070735].

## Introduction

1

Functional constipation (FC) has attracted widespread attention due to its high prevalence in the elderly population. Its incidence gradually increases with age (1, 2). 18.1–33.5% of people over 60 years old develop FC (3, 4). Furthermore, people over 80 years old have a higher risk (5). The diagnosis of FC is based on the Rome IV criteria (6). However, the etiology of constipation is usually multifactorial with aging, lack of physical activity, inadequate water and dietary fiber intake, dysbiosis, substance use, and so on (7–10). Long-term constipation will not only lead to colon diverticulum, perianal disease, colon melena, and other anorectal diseases (11), but also become a common predisposing factor for cardiovascular and cerebrovascular diseases such as myocardial infarction and cerebrovascular accident (12, 13). Some patients with severe constipation can also suffer from psychological disorders such as insomnia, irritability, depression, and obsessive-compulsive thoughts and behaviors (14–16). Therefore, as the aging of the population increases, this disease will seriously affect patients’ quality of life and bring a heavier burden to society.

Currently, the treatments of FC include lifestyle modification, transanal irrigation, pharmacological interventions, biofeedback therapy, and probiotics (17–21). Among these treatments, nonpharmacological management is the first step in the treatment of FC. When lifestyle modification and dietary interventions are ineffective, patients will seek help from medications. However, medication-assisted treatment is always limited in older patients (22). This is because most older adults have chronic diseases that require long-term treatment with other medications. Considering that drug interactions may further aggravate the disease, it is imperative to find a therapeutic method with certain efficacy and few side effects. It’s worth pointing out that acupuncture has been suggested to show potential for the treatment of FC. Recently, acupuncture has been widely used in the treatment of FC with relatively satisfactory results (23, 24). These results of the studies provide evidence for the efficacy of acupuncture in the treatment of FC. Nevertheless, the mechanisms underlying acupuncture in the treatment of FC are still incompletely fully understood. In addition, there are no reports of high-quality clinical studies on acupuncture for the treatment of FC in older people.

In recent years, many studies have focused on intestinal flora’s effects on human health, disease, and aging (25–27). It is noteworthy that dysbiosis of the intestinal microbiota is associated with constipation. It is reported that microbial diversity and abundance often decline in patients with constipation (28). In addition, the abundance of beneficial bacteria in the gut decreases with age (29). The gut microbiota of older people is less diverse compared to that of young people (30, 31). Meanwhile, any disturbance in the composition of the microbiota may lead to a reduction in the efficacy of the immune system, which is more pronounced in the elderly. In addition, cytokines play an important role in regulating the immune system’s interactions with the microbiota. As humans age, the function of innate and acquired immune both decreases, and pro-inflammatory mediators, such as acute-phase proteins, cytokines, and adhesion molecules in the bloodstream increase (32).

The selection and combination of acupuncture points, which is a key factor in the clinical effectiveness of acupuncture, is also a characteristic of acupuncture treatment. Meanwhile, we have observed in our clinic that some patients with FC have not only improved their constipation symptoms but also their moods after receiving acupuncture treatment. Consequently, considering this and the efficacy of the combination of acupuncture points and pathological characteristics of FC in older people, we designed this study. We hypothesize that acupuncture might improve clinical symptoms in older patients with FC by modulating intestinal microbial composition and inflammatory cytokines. Consequently, this trial aims to assess the efficacy and safety of acupuncture in treating FC in older people and to explore these mechanisms.

## Methods and analysis

2

### Study design

2.1

This study is a randomized, single-blind, sham acupuncture-controlled trial. It will be conducted at LongHua Hospital Shanghai University of Traditional Chinese Medicine. It has been registered on the China Clinical Trials Registry: ChiCTR2300070735. We will randomly recruit 98 patients who meet the enrollment criteria and randomly assign them to the acupuncture and sham acupuncture groups in a 1:1 ratio. The participants in both groups will be treated for 8 weeks and followed up for 12 weeks. In this clinical trial, we will strictly follow the Consolidated Standards of Reporting Trials (CONSORT) Statement and Standard Protocol Items: Recommendations for Interventional Trials (SPIRIT) (33). A flow chart of the trial procedure is shown in Figure 1 and the efficacy and mechanism diagram of the acupuncture study protocol is shown in Figure 2. Meanwhile, a detailed description of the study procedure and data collection is shown in Table 1.

**Figure 1 fig1:**
[figure not shown]
Trial flow chart. FC, functional constipation; CSBMs, Complete Spontaneous Bowel Movement; PAC-SYM, Patient Assessment of Constipation-Symptoms; PAC-QOL, Patient Assessment of Constipation Quality of Life Questionnaire; SAS, Self-Rating Anxiety Scale; SDS, Self-Rating Depression Scale.

**Figure 2 fig2:**
[figure not shown]
Efficacy and mechanism of acupuncture for functional constipation in the elderly.

**Table 1 tab1:** Schedule of enrolment, interventions and assessments.

Study period	Enrolment		Intervention period		Follow-up period	
Time point	Week −1	Week 0	Week 4	Week 8	Week 12	Week 20
Eligibility screening	×					
Sign informed consent	×					
Medical history	×					
Randomization		×				
Intervention						
Acupuncture			×	×		
Sham acupuncture			×	×		
Primary outcomes						
Treatment response rate				×		
Secondary outcomes						
Treatment response rate			×		×	×
The percentage of patients with ≥1 increase in mean weekly CSBMs from baseline			×	×	×	×
The mean weekly CSBMs change from the baseline			×	×	×	×
PAC-SYM		×		×		
PAC-QOL		×		×		
SAS		×		×		
SDS		×		×		
Weekly usage of emergency bowel medications		×	×	×	×	×
Adverse events			×	×		
Fecal microbiological		×		×		
Inflammatory cytokines		×		×		
Blinding assessment				×		

### Participants recruitment

2.2

The recruitment of participants for this study will be done by posting announcements and posters on official web-based information platforms. Interested participants can contact the researcher for initial screening through the phone number provided on the websites. Participants who initially meet the enrollment criteria will then have a face-to-face interview and baseline assessment with an independent researcher. In addition, 30 non-constipated older patients will also be recruited for this trial as a healthy control group who will receive no treatment. All participants will voluntarily sign a written informed consent prior to participation in this study and will be free to withdraw at any time during the study.

### Inclusion criteria

2.3

For FC patients, the inclusion criteria are as follows:

(1) Meet Rome IV Diagnostic Criteria for Constipation and TCM Diagnostic Criteria of constipation with yin deficiency syndrome; (2) No gender restriction, age 60–80; (3) FC that is classified as mild or moderate (34); (4) Have not used any medicine for constipation at least 4 weeks before treatment (except emergency treatment); (5) Those who can understand various evaluation scales, complete the evaluation and cooperate with the completion of the planned course of treatment; (6) Sign the informed consent.

For healthy subjects, the inclusion criteria are as follows:

(1) No gender restriction, age 60–80; (2) No constipation-related symptoms after comprehensive assessment for enrolment; (3) No significant gastrointestinal symptoms (e.g., abdominal pain, diarrhea, blood in the stool, constipation, abdominal distension, etc.) are reported in the 4 weeks before enrolment; (4) No medication to promote or inhibit gastrointestinal motility within 4 weeks before enrolment; (5) No mental and intellectual abnormalities, able to understand the provisions of each scale and complete the assessment; (6) Agree to participate in the study and sign the written informed consent.

### Exclusion criteria

2.4

For FC patients, the exclusion criteria are as follows:

(1) Irritable bowel syndrome and constipation caused by tumors, inflammatory reactions, endocrine and metabolic diseases, and drugs; (2) Constipation caused by organic diseases; (3) Patients with serious primary diseases such as heart, brain, liver, kidney and hematopoietic system, infectious diseases, tumors, and mental diseases; (4) Patients with ulcers, abscesses, skin infections, etc. at the acupuncture site; patients with metal allergies or severe fear of needles; (5) Have participated in other medical clinical trials over the past 2 months; (6) Those who used antibiotics or other drugs that may affect gut microbiota and inflammatory cytokines within 4 weeks before enrollment, which may affect the efficacy and judgment; (7) Patients who have received acupuncture treatment within the past 1 year.

For healthy subjects, the exclusion criteria are as follows:

(1) Patients with serious primary diseases such as heart, brain, liver, kidney and hematopoietic system, infectious diseases, tumors, and mental diseases; (2) Have metabolic-related diseases such as irritable bowel syndrome, abnormal thyroid function, or abnormal blood sugar/lipids; (3) Those who have used antibiotics or other drugs that may affect intestinal microbiota and inflammatory cytokines within 4 weeks before enrolment, thus affecting the efficacy and judgment; (4) Participation in other clinical medicine clinical trial studies within the last 2 months; (5) Patients who have received acupuncture treatment within the past 1 month, or will receive acupuncture treatment within the next 2 months.

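### Healthy controls and FC patients are selected by different metabolic and acupuncture wash-out rules, so an FC-versus-healthy biomarker difference may be confounded and cannot be put down to constipation alone

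*Protocol article*

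**What the plan says.** Section 2.2 adds a non-randomised reference group to the 98 randomised patients: "30 non-constipated older patients will also be recruited for this trial as a healthy control group who will receive no treatment".

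Section 2.4 then gives each population its own exclusion list. Two items differ in substance.

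- **Metabolic and endocrine status.** Healthy exclusion (2) reads "Have metabolic-related diseases such as irritable bowel syndrome, abnormal thyroid function, or abnormal blood sugar/lipids". FC exclusion (1) reads "Irritable bowel syndrome and constipation caused by tumors, inflammatory reactions, endocrine and metabolic diseases, and drugs". The first turns on the abnormality being present, the second on its having caused the constipation.
- **Prior acupuncture.** Healthy exclusion (5) reads "Patients who have received acupuncture treatment within the past 1 month, or will receive acupuncture treatment within the next 2 months". FC exclusion (7) reads "Patients who have received acupuncture treatment within the past 1 year".

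Other rules are the same or close in both groups: age 60–80, serious primary disease, irritable bowel syndrome (IBS), no other trial in the last 2 months, and a drug rule that for FC patients covers "antibiotics or other drugs that may affect gut microbiota and inflammatory cytokines within 4 weeks before enrollment".

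Section 2.10 plans stool and blood sampling at weeks 0 and 8 for the subjects, without splitting them by group.

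**The concern.** A reference group shows what constipation does to a marker only if it differs from the patients in constipation and little else. Here two further differences are written into eligibility. Controls are selected to be metabolically normal and FC patients are not. Controls may have had acupuncture between 1 and 12 months before entry and FC patients may not, although the Introduction hypothesises that acupuncture alters intestinal microbes and inflammatory cytokines.

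The metabolic difference is unlikely to touch only a few people. The Introduction says that "most older adults have chronic diseases that require long-term treatment with other medications".

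At stake is the reading of the 30 controls as the non-constipated reference for microbiota, SCFAs and the four cytokines (IL-6, IL-8, IL-10, TNF-α). Following section 2.4 exactly would still leave an unadjusted difference that mixes constipation with metabolic status and prior acupuncture.

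**Working it through.** **The plan's own figures.** The article gives no calculation for the 30 controls and no figure for this comparison. The only size used below is the randomised total: 39 per group, 39/(1 − 0.20) = 48.75, rounded up to 49, and 2 × 49 = 98.

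**Rules side by side (section 2.4).**

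| Item | FC patients | Healthy controls | Same? |
|---|---|---|---|
| Thyroid, glucose or lipid abnormality | Excluded only if it caused the constipation | Excluded whenever present | No |
| Past acupuncture | 1 year | 1 month | No |
| IBS | Excluded | Excluded | Yes |
| Drugs affecting microbiota or cytokines | 4 weeks | 4 weeks | Yes |
| Serious primary disease | Excluded | Excluded | Yes |

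An FC patient with a mild, untreated lipid or glucose abnormality not judged to cause the constipation passes every FC exclusion quoted here. The same person without constipation fails healthy exclusion (2). The shared rules do not close that gap, because such a person need have neither a serious disease nor a relevant drug.

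**Illustrative size of the metabolic part.** The documents give neither the prevalence of metabolic abnormality nor its effect on any marker, so both are assumed:

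- difference in prevalence, FC minus healthy: d = 0.2, 0.4 or 0.6 (about 0 in controls by rule);
- shift in a marker when the abnormality is present: s = 0.3, 0.5 or 0.8 SD;
- all 98 FC patients and all 30 controls sampled, and no true constipation effect.

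False standardised difference: b = d × s.

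Standard error: SE = √(1/98 + 1/30) = √(0.0102 + 0.0333) = 0.209 SD.

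Chance of two-sided p < 0.05: 1 − Φ(1.96 − b/SE) + Φ(−1.96 − b/SE).

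| d | s = 0.3 | s = 0.5 | s = 0.8 |
|---|---|---|---|
| 0.2 | b = 0.06, 6.0% | b = 0.10, 7.7% | b = 0.16, 12.0% |
| 0.4 | b = 0.12, 8.9% | b = 0.20, 16.0% | b = 0.32, 33.5% |
| 0.6 | b = 0.18, 13.9% | b = 0.30, 30.1% | b = 0.48, 63.3% |

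The result runs from negligible (6%, against a nominal 5%) to serious (63%).

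**Prior acupuncture.** No number can be attached. The documents do not say how many controls would have had recent treatment or how long any biomarker effect lasts.

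**The case against.** The strongest objection is that the article never states an FC-versus-healthy comparison. Table 1 has no healthy-group entry, section 2.13 lists no such contrast, and the limitations paragraph of the Discussion speaks of samples from FC patients only. The stated mechanism aim, how acupuncture works, is addressed by acupuncture versus sham. This stands as far as it goes: the comparison is inferred. The inference is still a fair one. An untreated group, called a healthy control group and screened for drugs affecting microbiota and cytokines, has no other evident use.

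A second objection is that an analysis plan, not shown, could adjust or restrict. This also stands in part, and it rules out the reading that the two influences can never be separated. Restriction can separate metabolic status. Covariate adjustment is weaker: with no metabolically abnormal controls, it must take the metabolic effect from FC patients and assume it is the same without constipation.

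Third, the shared drug rule may already bar some FC patients on long-term metabolic medication, so a reader should not infer that every patient with treated diabetes is eligible. That is right, and it lowers the plausible prevalence difference without bringing it to zero.

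Fourth, a reader might take the 12-week follow-up as evidence that acupuncture effects on biomarkers persist past 1 month. It is not. The later visits record bowel movements and rescue use, and biomarkers are sampled only at weeks 0 and 8. The longer FC wash-out may also serve blinding against sham, which controls do not need. The unequal wash-out is therefore a possible source of bias, not a demonstrated one.

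**Conclusion.** The point holds in limited form. Section 2.4 applies different metabolic and acupuncture rules to the two populations, and an FC-versus-healthy biomarker difference may be confounded by both. It cannot be attributed to constipation alone. The documents do not support the stronger reading that such a difference says nothing about constipation, because the bias may be small and the shared exclusions remove part of it.

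The 6% to 63% range covers the metabolic part only. It rests on the assumed prevalence differences and shifts and on all 98 patients being sampled. It shows what could happen and does not estimate what will.

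The reach is narrow: one exploratory, non-randomised comparison. The primary outcome, the secondary outcomes and the randomised week 0 to week 8 biomarker comparison are untouched. This is a cheap improvement, best made before controls are enrolled, since eligibility cannot be corrected afterwards.

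**What to change.** 1. In section 2.4, give healthy subjects the same 1-year look-back for acupuncture as FC patients, and keep their existing 2-month forward window.
2. State the FC-versus-healthy comparison of microbiota, SCFAs and cytokines, and define its FC set as patients who also meet healthy exclusion (2). Label the comparison using all FC patients descriptive.

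Loosening the healthy metabolic exclusion and frequency-matching instead is a debatable design choice. If healthy exclusion (2) were replaced by the serious-disease rule, the explicit IBS exclusion for controls would also go.

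**Cost.** Recruitment of the 30 controls may be slightly slower. Thyroid, glucose and lipid status must be known for FC patients. The FC set in this one comparison shrinks: if 20% to 60% of 98 were set aside, about 78 to 39 would remain, and the SE would rise from 0.209 to between √(1/78 + 1/30) = 0.215 and √(1/39 + 1/30) = 0.243 SD. That is a modest loss of precision for removing the metabolic difference. The randomised comparison does not change.

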### Randomization and allocation concealment

2.5

Participants in the experiment will be divided into two groups by using the method of randomization. Random numbers will be obtained through the “Proc plan” function of SAS 9.4 statistical analysis software by the Clinical Research Center of LongHua Hospital, Shanghai University of Traditional Chinese Medicine. The treatment allocation codes will be placed in sequentially numbered opaque envelopes by an independent study staff member. Depending on the order of the patients’ visits, the investigator will select the envelopes. All participants will be informed that they have an equal chance of being assigned to either the acupuncture group or the sham acupuncture group. Moreover, to ensure the implementation of shielding, all researchers will receive training on the implementation of this research specification many times before the implementation of the experiment and strictly abide by the principle of separation of departments.

### Blinding

2.6

The single-blind method is used in this trial. With the exception of the acupuncturist, participants, and all study personnel, including statisticians, outcome assessors, sample collectors and data analysts, are unaware of group assignments. To ensure the successful implementation of the blind method, patients are required to wear eye masks during treatment and it is performed in a closed treatment unit. And they will be told not to remove the eye masks during the treatment. In addition, after the last treatment, an independent assessor will provide all participants with three options by asking questions: acupuncture, sham acupuncture, and uncertainty. Then the answers will be recorded on a case report form (CRF). Statistical analysis of patients’ options is performed to assess the success of the blind method implementation.

### Intervention

2.7

#### Acupuncture group

2.7.1

Participants in the intervention group will receive acupuncture treatment at Zhao Hai (KI 6), Da Zhong (KI 4), Tai Xi (KI 3), Tian Shu (ST 25), and Shang Ju Xu (ST 37). All acupoints are taken on both sides [Acupoint Location: refer to *The Location of Acupoints: State Standard of the People’s Republic of China* (GB/T 12346–2021)]. All acupoints will be routinely sterilized, and the acupuncture method for each point is shown in Table 2. After the insertion of the needles, manipulations of lifting, twirling, and thrusting are performed on all needles to reach de qi, which is a sensation typically associated with needling including soreness, numbness, swelling, heaviness, and other feelings. This is considered to be an important component of the therapeutic effect of acupuncture (35). The sterile acupuncture needles (size 0.25*40 mm and 0.30*50 mm) that will be used are from Wuxi Jiajian Medical Equipment Co.

**Table 2 tab2:** The locations and manipulations of acupoints in the intervention group.

Acupoint	Location	Manipulation
Zhao Hai (KI 6)	On the medial side of the foot, 1 cun below the tip of the medial malleolus, in the depression at the lower edge of the medial malleolus	Insert the needle perpendicularly for 0.5–0.8 cun.
Da Zhong (KI 4)	On the medial side of the foot, posterior and inferior to the medial malleolus, on the upper border of the calcaneus, in the depression on the medial anterior border of the calcaneal tendon attachment	Insert the needle perpendicularly for 0.3–0.5 cun.
Tai Xi (KI 3)	On the posteromedial side of the ankle, in the depression between the tip of the medial malleolus and the calcaneal tendon	Insert the needle perpendicularly for 0.5–1.0 cun.
Tian Shu (ST 25)	On the upper abdomen, horizontal to the umbilicus, 2 cun lateral to the anterior midline	Insert the needle perpendicularly for 1.0–1.5 cun.
Shang Ju Xu (ST 37)	On the outside of the calf, 6 cun below ST 35(Du Bi), on the line connecting ST 35(Du Bi) and ST 41 (Jie Xi)	Insert the needle perpendicularly for 1.0–2.0 cun.

